### Analysis

The primary outcome measure is clinical resolution on day 7 as defined above. We will compare the proportion of children meeting the definition of clinical resolution using intention-to-treat analysis (ITT), as well as per-protocol analysis, as non-inferiority trials that use only ITT can be biased towards finding non-inferiority [39]. The per-protocol population will consist of all randomised patients who have adhered to the allocated treatment, were not lost to follow-up, and who have no major protocol deviations. All participants with complete outcome information at day 7 will be included. For protocol deviations where participant data are available, these will be analysed and the impact of their inclusion assessed and reported.

Sensitivity analyses will describe the impact of the following alternative assumptions: (1) missing = clinical failure; (2) missing = clinical success; (3) extrapolation from days 2 − 4 telephone interview; (4) best case for watchful waiting; and (5) worst case for watchful waiting. A secondary per-protocol analysis (accounting for non-adherence and change in treatment) will be done to describe any short-term benefits and harms associated with antibiotic use.

Non-inferiority of watchful waiting compared with antibiotic treatment will be accepted if the lower bound of the 95 % CI around the estimated difference in the primary endpoint rates does not exceed 10 %.

Data analysis will include analysis using Fisher’s exact and Chi-square tests for categorical outcomes, and parametric and non-parametric tests for continuous measures, as required. The difference in the primary endpoint between the two groups will be expressed as a risk difference. Where appropriate, odds ratios (ORs) will be calculated and will include both unadjusted (crude) and adjusted ORs. Adjusted ORs will be obtained using multivariable logistic regression, adjusting for baseline covariates. Time to resolution of AOM symptoms will be modelled using a multilevel Cox (proportional hazards) regression analysis and graphically displayed using Kaplan-Meier curves. Secondary analyses by stratification factors (recruitment site and age) will be carried out, numbers permitting.

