### Design

We are using a non-inferiority, open-label, randomised controlled trial (RCT) design. Non-inferiority studies seek to determine if a new treatment is no worse than a reference treatment by a predetermined margin. The new treatment is recommended if it is similar or better than the previous treatment, usually on the premise that the new treatment has other advantages over the reference treatment [31]. Children will be randomised to watchful waiting or immediate antibiotic therapy, stratified by study site and age of child (2 − 6 years and 7 − 16 years), using the National Health and Medical Research (NHMRC) Clinical Trial Centre Interactive Voice Response System (IVRS). It is not possible to blind the patient or treating staff. Outcome measurements will be verified by blinded assessment of tympanometry and video-pneumatic otoscopy (VO) data by an otolaryngologist and analysis will be blinded.

For practical reasons, the participating sites will commence staggered recruitment, commencing in two sites per block, 6 months apart. We will undertake cost-effectiveness analysis and a qualitative study in conjunction with the RCT as an integral part of the study design, with planning for both having commenced at inception [32]. A Data Safety Monitoring Board will oversee the conduct of the trial.

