### Cost-effectiveness data collection and analysis

As a secondary outcome measure, we will assess the cost-effectiveness of watchful waiting compared to immediate antibiotic prescription, as measured through the incremental cost-effectiveness ratio (ICER). The ICER is defined as:$$ "\mathrm{ICER}"=\left({\mathrm{C}}_{\_2}-{\mathrm{C}}_{\_1}\right)/\left({\mathrm{Q}}_{\_2}-{\mathrm{Q}}_{\_1}\right) $$

where *C*_*i*_ and *Q*_*i*_ denote costs and Quality-adjusted Life Years (QALYs) [40] associated with the treatment received in trial arm *i*, and *i* is 1 for antibiotic treatment and 2 for watchful waiting.

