## Discussion

The WATCH trial will answer the important clinical question: whether watchful waiting is (or is not) inferior to immediate antibiotic therapy for urban Aboriginal children with AOM who are at low risk of complications. We will assess the cost-effectiveness of the two approaches and qualitatively examine the acceptability of the alternate approaches to management of AOM to parents and carers, and health care providers. Furthermore, we will examine experiences of the trial process itself in order to inform future RCT studies in Aboriginal health settings.

This trial will make an important contribution to the evidence base for the safe management of AOM in urban Aboriginal children. Australian guidelines for the management of AOM have recently been updated [5] and Aboriginal and Torres Strait Islander children living in urban settings are no longer classified as high risk for complications of AOM, and thus health care providers are advised they should be treated with watchful waiting. This requires a change in clinical practice. The expert consensus guideline advice has been extrapolated from studies in low-risk, developed countries internationally. There have been no studies into the relative effectiveness of a watchful waiting approach for urban Aboriginal and Torres Strait Islander children, nor of attitudes of carers and health care providers to this approach.

Research undertaken with Aboriginal and Torres Strait Islander people must have net benefits for communities, incorporate community research control, be conducted in a manner sensitive to the cultural principles of Aboriginal society, be appropriately resourced and enhance the skills and knowledge of the Aboriginal and Torres Strait Islander people, communities and organisations that are participating in the project [34]. This study has been designed with awareness and commitment to these guiding principles and to the flexibility required to undertake a randomised controlled trial in Aboriginal and Torres Strait Islander health settings.

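### The printed non-inferiority rule lacks a minus sign and an order of subtraction, and is valid in neither direction

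*Protocol article*

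**What the plan says.** The decision rule for the primary endpoint stands in one sentence of the protocol article, under Analysis. It opens "Non-inferiority of watchful waiting compared with antibiotic treatment will be accepted if the lower bound of the 95" % and continues "CI around the estimated difference in the primary endpoint rates does not exceed" 10 %. The same section says of the effect measure only that "The difference in the primary endpoint between the two groups will be expressed as a risk difference". Neither sentence gives an order of subtraction.

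The endpoint is the proportion of children with clinical resolution at day 7 (Primary outcome), so a higher rate is better. The Design section describes the aim of a non-inferiority study as showing that a new treatment is "no worse than a reference treatment by a predetermined margin", and Sample size and power sets that margin at 10 %. Neither section restates the acceptance rule, and no other section does.

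The only place that fixes an order of arms is the cost-effectiveness section. There the ratio takes arm 2 minus arm 1, and the index "is 1 for antibiotic treatment and 2 for watchful waiting". That convention is given for costs and QALYs, not for the primary endpoint.

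**The concern.** For a success rate there are two equivalent ways to write a 10-point non-inferiority rule:

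- watchful waiting minus antibiotic: the **lower** limit must lie above **-10** points;
- antibiotic minus watchful waiting: the **upper** limit must lie below **+10** points.

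The printed sentence takes the lower limit from the first and the positive threshold from the second. Read as watchful waiting minus antibiotic, it is met by almost any result, and fails only when watchful waiting looks much better. Read as antibiotic minus watchful waiting, it asks only that a deficit of 10 points or less has not been ruled out, which reverses the burden of proof.

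This is the pre-specified criterion for the trial's main conclusion. Applied as printed, it gives no control over a false claim of non-inferiority. Applied as presumably intended, the reader has to supply both the sign and the direction.

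**Working it through.** **Inputs.** From Sample size and power: 198 evaluable children per arm, 80 % power, 10-point margin, 5 % significance level (sidedness not stated), 80 % improvement in both arms, 20 % dropout, 495 in total. From Analysis: 95 % CI, lower bound, threshold 10 %. Assumptions for this check: a Wald interval for the risk difference, two-sided unless noted, and 80 % resolution on antibiotics.

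**Step 1: reproduce the sample size.**

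n per arm = (z₁₋α + z₀.₈₀)² × [0.8 × 0.2 + 0.8 × 0.2] / 0.10²

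- One-sided 5 %: (1.645 + 0.842)² × 0.32 / 0.01 = 197.8, so 198. Total 396 / 0.80 = 495. Both stated figures reproduce.
- One-sided 2.5 % (the level of a two-sided 95 % CI): (1.960 + 0.842)² × 0.32 / 0.01 = 251.2, so 252. Total 504 / 0.80 = 630. This does not reproduce.

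The sample size therefore rests on the 10-point margin at one-sided 5 %, and does not depend on the wording of the acceptance sentence.

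**Step 2: what the literal rule does with expected results.** The standard error is √[p_w(1 − p_w)/198 + 0.8 × 0.2/198], where p_w is the watchful-waiting rate. The interval is the difference ± 1.96 × SE.

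| True deficit of watchful waiting | SE (points) | CI, watchful waiting − antibiotic | CI, antibiotic − watchful waiting |
|---|---|---|---|
| 10 points | 4.32 | -18.5 to -1.5 | 1.5 to 18.5 |
| 20 points | 4.49 | -28.8 to -11.2 | 11.2 to 28.8 |
| 30 points | 4.55 | -38.9 to -21.1 | 21.1 to 38.9 |

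In the third column every lower limit is below +10, so each result is accepted. In the last column the lower limit is below 10 only in the first row.

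**Step 3: probability of acceptance.** Summing over all pairs of binomial counts (198 per arm, antibiotic rate 80 %, two-sided 95 % interval):

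| True deficit | Intended rule (watchful waiting − antibiotic, lower limit > -10) | Literal, watchful waiting − antibiotic | Literal, antibiotic − watchful waiting |
|---|---|---|---|
| 0 points | 70.6 % | 100 % | 100 % |
| 10 points | 2.6 % | 100 % | 97.4 % |
| 15 points | 0.1 % | 100 % | 79.4 % |
| 20 points | about 0 % | 100 % | 39.6 % |
| 25 points | about 0 % | 100 % | 9.3 % |
| 30 points | about 0 % | 100 % | 0.9 % |

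With a one-sided 95 % bound (z = 1.645) the 10-point row becomes 5.0 %, 100 % and 94.9 %, so the conclusion does not turn on sidedness.

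**Step 4: single results.**

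- Antibiotic 158/198, watchful waiting 99/198. Watchful waiting minus antibiotic is -29.8 points (CI -38.7 to -20.9). The lower limit does not exceed +10, so the literal rule accepts.
- Antibiotic 158/198, watchful waiting 121/198. Antibiotic minus watchful waiting is 18.7 points (CI 9.9 to 27.5). The lower limit is 9.9, so the literal rule accepts.
- Under the intended rule, with 80 % on antibiotics, the largest observed deficit accepted is about 2.0 points.

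**Step 5: power of the intended rule at 198 per arm.** With equal arms at 80 %, SE = √(0.32/198) = 0.0402. A two-sided 95 % interval gives Φ(0.10/0.0402 − 1.96) = 70.1 % by normal approximation and 70.6 % by enumeration. One-sided 5 % gives 80.0 %.

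**The case against.** The strongest reply is that the intent can be recovered. The Design section gives the concept, the margin is 10 %, the sentence speaks of watchful waiting compared with antibiotic treatment, and it names the lower bound of a success-rate difference. Together these point to watchful waiting minus antibiotic with a shortfall of no more than 10 points, and the 10 % can be read as the size of the shortfall. An order of subtraction is also a detail that an article may leave to the full protocol or analysis plan. Much of this stands: it makes the intended rule fairly clear and lowers the practical risk. It does not make the printed rule correct. The article chose to state the criterion, stated it wrongly, and nowhere else states it correctly.

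Three stronger readings are tempting, and the documents do not support them.

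- A reader might infer that the trial would actually be analysed this way. Nothing shows that. The acceptance probabilities describe the sentence as printed, not the likely conduct of the analysis.
- A reader might infer that the rule accepts deficits of up to 30 points whichever way the difference is taken. That holds only for watchful waiting minus antibiotic. In the other direction acceptance falls to 39.6 % at 20 points and 0.9 % at 30.
- A reader might take the Discussion's phrase "whether watchful waiting is (or is not) inferior to immediate antibiotic therapy" to mean that missing the margin will be reported as inferiority. That phrase poses the clinical question in general prose. It is not a decision rule, and no section says that a failed test will be reported in that way.

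**Conclusion.** The point holds as an error in the written decision rule for the primary endpoint. As printed, the rule is valid under neither order of subtraction. At a true 10-point deficit it accepts in about 100 % or 97 % of trials, depending on direction, against 2.6 % for the rule that was probably meant. At 20 points it accepts in 100 % or 40 %, and only watchful waiting minus antibiotic still accepts routinely at 30 points.

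These figures assume 198 evaluable children per arm, 80 % resolution on antibiotics and a two-sided 95 % Wald interval. The choice between a one-sided and a two-sided interval does not change the conclusion on sign and direction. It does matter for power, and so has to be settled when the sentence is rewritten. Because this sentence governs the trial's main claim and is cheap to correct, it should be corrected.

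**What to change.** Replace the acceptance sentence under Analysis with:

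> The difference is the resolution rate under watchful waiting minus that under immediate antibiotics. Non-inferiority is accepted if the lower limit of the 95 % CI is greater than -10 percentage points.

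Then state whether the 95 % CI is one-sided or two-sided, and reconcile this with Sample size and power:

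- **One-sided 95 % bound (5 %):** 198 per arm and 80 % power stand as printed.
- **Two-sided 95 % interval (2.5 % in the relevant tail):** 198 per arm gives about 71 % power, and the stated power must be restated. Keeping 80 % would need 252 per arm, or 630 in total with 20 % dropout.

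Correcting the sign and direction is a short text change that needs no new data, no more children and no loss of power. The power question comes from the existing pairing of a 5 % significance level with a 95 % CI. The correction does not create it, but makes it visible. If an analysis plan exists, its wording should be checked against the corrected sentence.

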### Sample size and power

With 198 children in each arm of the study, the study will have 80 % power to detect a non-inferiority margin of up to 10 % at a significance level of 5 %, assuming a clinical improvement rate of at least 80 % in both study groups [38]. Allowing for a dropout rate of up to 20 % at days 5 − 10, the total sample size required is 495 children.

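### The printed non-inferiority rule sets no order of subtraction and compares the lower confidence bound with plus 10 %, so it is wrong as written under either order

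*Protocol article*

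**What the plan says.** The Analysis section of the protocol article gives the trial's only acceptance criterion. Non-inferiority "will be accepted if the lower bound of the 95" % CI "around the estimated difference in the primary endpoint rates does not exceed" 10 %. The same section fixes the scale, "The difference in the primary endpoint between the two groups will be expressed as a risk difference", and the endpoint, "We will compare the proportion of children meeting the definition of clinical resolution". A larger proportion is therefore a better result. The section does not say which arm is subtracted from which.

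The Sample size and power section gives the margin only as a size: the trial is to "detect a non-inferiority margin of up to 10" %, at a 5 % significance level whose sidedness is not stated. The Abstract says the same. The only explicit order of subtraction is in the cost-effectiveness section, where the index "is 1 for antibiotic treatment and 2 for watchful waiting" makes the ICER differences watchful waiting minus antibiotics. That convention is not extended to the primary endpoint.

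**The concern.** A non-inferiority rule needs three things to agree: the order of subtraction, the confidence limit that is tested, and the sign and direction of the threshold. Here the order is missing, and the limit and threshold do not fit together under either order.

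- **Watchful waiting minus antibiotics.** The lower bound is the right limit, but it has to lie above -10 points. As printed it has only to be no larger than +10, which any deficit satisfies.
- **Antibiotics minus watchful waiting.** A threshold of +10 is right, but the upper bound is the one that must stay below it. A lower bound below +10 does not exclude a loss of more than 10 points.

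Adding a minus sign alone would not mend the sentence. A lower bound that does not exceed -10 is one at or below -10, which is the result that should fail. The direction of the comparison has to change as well.

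At stake is whether the pre-specified criterion can be applied without guessing, in an open-label trial whose result is meant to inform whether immediate antibiotics are withheld.

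**Working it through.** **Inputs.** From Sample size and power: 198 per arm, 80 % resolution in both arms, margin 10 points, 80 % power, 5 % significance, 20 % dropout. From Analysis: lower bound of a 95 % CI for a risk difference. Assumptions for this check: a Wald interval, 198 evaluable children per arm, antibiotic resolution held at 80 %.

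**1. The plan's own figure.** n per arm = (z₁₋α + z₁₋β)² × [p(1-p) + p(1-p)] / margin², and the bracket is 2 × 0.16 = 0.32.
- One-sided α = 0.05: (1.645 + 0.842)² × 0.32 / 0.01 = 197.8, so 198. This matches.
- One-sided α = 0.025: (1.960 + 0.842)² × 0.32 / 0.01 = 251.2, so 252. This does not match.
- Dropout: 396 / 0.80 = 495. This matches.

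The sample size therefore rests on a one-sided 5 % test.

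**2. Intervals at 198 per arm.** SE = √{[p_W(1-p_W) + p_A(1-p_A)] / 198}; interval = difference ± 1.96 × SE.

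| Watchful waiting vs antibiotics | SE | Watchful waiting minus antibiotics (points) | Antibiotics minus watchful waiting (points) |
|---|---|---|---|
| 70 % vs 80 % | 0.0432 | -18.5 to -1.5 | +1.5 to +18.5 |
| 60 % vs 80 % | 0.0449 | -28.8 to -11.2 | +11.2 to +28.8 |
| 50 % vs 80 % | 0.0455 | -38.9 to -21.1 | +21.1 to +38.9 |

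In the third column every lower bound is below +10, so the printed rule accepts all three rows, although in the last two the whole interval lies beyond the margin. In this order the rule fails only when watchful waiting is observed to be better by roughly 16 points or more.

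In the fourth column the printed rule rejects the last two rows but accepts the first, where the upper bound is +18.5. The largest observed deficit it accepts, with 158/198 resolved on antibiotics, is 121/198 on watchful waiting: a deficit of 18.7 points with lower bound +9.9. At 120/198 the lower bound is +10.4 and the rule rejects.

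**3. Chance of accepting non-inferiority.** Let d be the true watchful waiting minus antibiotics difference.
- Printed rule, watchful waiting minus antibiotics: Φ[(0.10 - d)/SE + 1.96]
- Printed rule, antibiotics minus watchful waiting: Φ[(0.10 + d)/SE + 1.96]
- Corrected rule, lower limit of a two-sided 95 % interval above -10: Φ[(0.10 + d)/SE - 1.96]

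| True d (points) | Printed, watchful waiting minus antibiotics | Printed, antibiotics minus watchful waiting | Corrected |
|---|---|---|---|
| 0 | about 100 % | about 100 % | 70.1 % |
| -10 | about 100 % | 97.5 % | 2.5 % |
| -20 | about 100 % | 39.6 % | 0.001 % |
| -30 | about 100 % | 0.7 % | about 0 |

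Example, second rule at d = -20: (0.10 - 0.20)/0.0449 + 1.96 = -0.26, and Φ(-0.26) is about 0.40.

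**4. Power once the sign is corrected.** With d = 0, SE = √(0.32/198) = 0.0402 and 0.10/0.0402 = 2.487.
- One-sided 5 %: Φ(2.487 - 1.645) = 80.0 %.
- Lower limit of a two-sided 95 % interval: Φ(2.487 - 1.960) = 70.1 %.

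The second is below the stated 80 %. Reaching 80 % that way needs 252 per arm, or 504 / 0.80 = 630 in total.

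**The case against.** The strongest reply is that the intended rule can be recovered from the document. The Design section defines non-inferiority as being no worse than the reference by a set margin, Sample size and power puts that margin at 10 %, and the acceptance sentence names watchful waiting compared with antibiotics and uses the lower bound, which is the relevant limit only for watchful waiting minus antibiotics. Read as a limit on the size of the deficit, the sentence is loose shorthand for a lower bound not below -10 points. The literal reading contradicts the Design section, and the near-100 % acceptance follows mechanically from comparing a negative bound with +10. This reply stands as to intent. It does not make the printed sentence correct, and no other place restates it with a sign and an order.

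Three stronger readings are tempting, and the document does not support them.

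- **That the trial would in practice accept a strategy 20 to 30 points worse.** Nothing shows that the analysis would be run on the literal wording, and the stated margin points the other way.
- **That acceptance at 20 to 30 points worse holds whatever the order.** It holds for watchful waiting minus antibiotics. In the other order acceptance is about 40 % at 20 points and under 1 % at 30, and the fault is the wrong bound.
- **That either analysis set could be picked to claim success.** The acceptance sentence names no set, but the section commits to both intention-to-treat and per-protocol analyses and gives its reason, "as non-inferiority trials that use only ITT can be biased towards finding non-inferiority". That reason argues against relying on intention-to-treat alone. Whether both must pass is a detail that an analysis plan may settle.

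**Conclusion.** The decision rule is wrong as written and should be corrected. Under either order of subtraction the literal sentence fails to exclude a loss greater than the 10-point margin: at a true deficit of exactly 10 points it accepts about 100 % or 97.5 % of the time, against 2.5 % for the corrected rule with a two-sided 95 % interval. This is an error of wording in the trial's single acceptance criterion. It is not a finding about how the data would be analysed.

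The acceptance figures assume Wald intervals, 198 evaluable children per arm and 80 % resolution on antibiotics. The conclusion that the limit and threshold do not match needs none of these.

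Correcting the sign does not settle a linked mismatch. The sample size reproduces only at one-sided 5 %, while a lower 95 % bound in its usual two-sided sense is a one-sided 2.5 % test, with power of about 70 % if both true rates are 80 %.

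**What to change.** Replace the acceptance sentence in the protocol, and in the analysis plan if it carries the same wording, with:

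> Difference = resolution proportion (watchful waiting) minus resolution proportion (immediate antibiotics). Non-inferiority is concluded if the lower limit of the 95 % CI is greater than -10 percentage points.

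In the same edit, state whether the interval is one- or two-sided and make it agree with Sample size and power:

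- A one-sided 95 % limit keeps 198 per arm and 80 % power, with a 5 % chance of acceptance at a true deficit of 10 points.
- The lower limit of a two-sided 95 % interval lowers that chance to 2.5 %. The stated power then has to be given as about 70 %, or the target raised to 252 per arm (630 in total with 20 % dropout).

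The sign and order correction costs one sentence and no data. The choice of sidedness costs either the stricter error rate, or power or recruitment, and should be made before results are known.

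Requiring the criterion to be met in both the intention-to-treat and per-protocol analyses would follow the protocol's own reasoning. It is secondary, may be left to the analysis plan, and would lower the chance of success somewhat further.

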### Study setting

The study is a multi-centre study with six participating sites, all of which are in urban settings, including: five Aboriginal Community Controlled Health Services (ACCHSs); and one Indigenous Health Service. ACCHS are services dedicated to health care delivery for Aboriginal Australians and are run by the local Aboriginal communities for the local Aboriginal community and are also known as Aboriginal Medical Services. The Indigenous Health Service has different governance to the ACCHSs, being a state government-supported general practice, which provides primary health care to Aboriginal and Torres Strait Islander peoples. For the purposes of this publication the ACCHSs and the Indigenous Health Service are collectively referred to as health services. The health services are in three states in eastern Australia; two in Queensland (Brisbane), three in New South Wales (Newcastle and Sydney) and one in the Australian Capital Territory (Canberra).

Participants will be recruited from the clients attending the health services. We will obtain informed consent from each participant or their guardian.

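### Randomisation is stratified by site and age, but the Analysis section does not carry these factors into the primary risk difference, and the only adjusted estimate it describes is an odds ratio, which cannot be read against the 10-point margin

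*Protocol article*

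**What the plan says.** All references are to the protocol article.

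- **Design.** Children are randomised "stratified by study site and age of child", with two age bands (2–6 and 7–16 years). Study setting adds: "The study is a multi-centre study with six participating sites".
- **Analysis, decision rule.** Watchful waiting is accepted as non-inferior if the "lower bound of the 95 % CI around the estimated difference in the primary endpoint rates does not exceed 10" %. The rule is on the absolute scale.
- **Analysis, effect measure.** "The difference in the primary endpoint between the two groups will be expressed as a risk difference". The sentence does not say whether that difference is crude, stratified or adjusted.
- **Analysis, tests.** A general list names Fisher's "exact and Chi-square tests for categorical outcomes".
- **Analysis, adjustment.** "Where appropriate, odds ratios (ORs) will be calculated and will include both unadjusted (crude) and adjusted ORs". Then: "Adjusted ORs will be obtained using multivariable logistic regression, adjusting for baseline covariates". The covariates are not named.
- **Analysis, stratification factors.** "Secondary analyses by stratification factors (recruitment site and age) will be carried out, numbers permitting". This is the only place in the section where site and age are mentioned.

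**The concern.** An analysis normally reflects the way the groups were formed. Here the factors that constrained the allocation are given a secondary, conditional role, and nothing links them to the estimate that decides the trial. Two consequences follow.

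1. **Precision.** Stratified allocation balances the arms on site and age, so the risk difference varies less from trial to trial than the simple two-sample standard error implies, provided that site and age predict resolution. A crude interval does not take credit for this and is somewhat too wide. They may well be predictive. Resolution is judged by unblinded clinicians by one of two routes (Primary outcome), nurse practitioners diagnose and treat at one site (Trial status), and the diagnostic criteria differ for children aged 2 to 3 years (Inclusion).
2. **Scale.** The margin is 10 percentage points. The only adjusted estimate described is an odds ratio, and no single odds ratio stands for 10 points. If chance imbalance made readers want an adjusted answer to the non-inferiority question, the analysis described could not give one.

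**Working it through.** **Inputs from the article.** 198 evaluable children per arm, 80% resolution in both arms, margin 10 points, 80% power, significance level 5%, 20% dropout (Sample size and power); 6 sites and 2 age bands (Study setting, Design). The article gives no resolution rates by site or age, so every between-stratum spread below is an assumption.

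**Step 1: the plan's own figure.** n per arm = 2p(1−p)(z₀.₉₅ + z₀.₈₀)²/0.10² = 0.32 × (1.645 + 0.842)²/0.01 = 197.8, so 198. With dropout, 396/0.80 = 495. Both figures reproduce at one-sided 5%. The formula contains no term for strata.

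**Step 2: can an odds ratio be read against the margin?** For a control rate p, a 10-point loss is OR = [(p − 0.10)/(1.10 − p)] / [p/(1 − p)].

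| Control rate | OR for a 10-point loss |
|---|---|
| 70% | (0.60/0.40)/(0.70/0.30) = 0.64 |
| 80% | (0.70/0.30)/(0.80/0.20) = 0.58 |
| 90% | (0.80/0.20)/(0.90/0.10) = 0.44 |
| 95% | (0.85/0.15)/(0.95/0.05) = 0.30 |

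Conversely, an OR of 0.583 is a loss of 12.4 points at 70%, 10.0 at 80% and 6.0 at 90%. The sample size section assumes a rate of at least 80%, which leaves much of this range open.

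**Step 3: what does a crude interval cost?** Take 12 equal strata with mean rate 0.80 and between-stratum variance V of the rates.

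- Crude standard error: √[2 × 0.16/198] = 0.0402.
- True standard deviation under stratified allocation: √[2 × (0.16 − V)/198].
- Power with the crude interval: Φ[(0.10 − z × 0.0402)/SD].
- Power with the stratified interval: Φ[0.10/SD − z].

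With a two-sided 95% CI (z = 1.96) and true difference 0:

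| Assumed span of stratum rates | V | SD | Power, crude CI | Power, stratified CI | Gain (points) |
|---|---|---|---|---|---|
| 0 points | 0 | 0.0402 | 70.1% | 70.1% | 0 |
| 15 points (72.5–87.5%) | 0.0018 | 0.0400 | 70.2% | 70.6% | 0.4 |
| 24 points (68–92%) | 0.0046 | 0.0396 | 70.4% | 71.4% | 1.0 |
| 33 points (63.5–96.5%) | 0.0087 | 0.0391 | 70.6% | 72.5% | 1.9 |

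Simulation agrees (40,000 trials per case, 192 per arm after rounding): at the 24-point span power is 69.3% crude and 70.2% stratified, and at the 33-point span 69.6% and 71.3%.

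**Step 4: wider spreads.** Two sets of simulations used 396 evaluable children, a two-sided 95% CI, and a crude Wald interval against a Mantel-Haenszel risk difference with Sato variance.

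| Assumed site rates and age effect | First set, crude / stratified | Second set, crude / stratified |
|---|---|---|
| 76–86%, 5 points | both about 70% | 71.8% / 72.2% |
| 65–95%, 15 points | 67.6% / 70.4% | 71.3% / 74.7% |
| 55–97%, 20 points | 65.6% / 71.2% | 64.1% / 70.4% |

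The absolute levels differ between the sets, but the gains agree: about 0 to 0.4, 2.8 to 3.4, and 5.6 to 6.3 points. In the first set's middle case the crude standard error averaged 0.0417 against a true SD of 0.0401, so the interval was about 4% too wide. That standard error implies a mean rate of about 78% (0.0417² × 99 = 0.172 = p(1−p)), slightly below the article's 80%.

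**Step 5: is the crude interval safe?** At a true 10-point deficit, in the 40,000-trial simulations of step 3, the crude interval declared non-inferiority in 2.1 to 2.5% of trials (nominal 2.5%), or 4.8 to 5.1% when read at one-sided 5%. The lowest figures came with the widest spread. Type I error is not inflated.

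**The case against.** The strongest reply is that this is a condensed article. It never says that the primary risk difference is crude: in the Analysis section the words for unadjusted and adjusted apply to odds ratios alone. An analysis plan not shown may specify a stratified difference, and the unnamed baseline covariates may include site and age. This stands in part. A reader might infer that the trial has committed itself to an unadjusted primary analysis; the text makes that the natural reading but does not state it. What remains is what the section does state: it gives site and age one role, which is secondary and conditional, and it attaches adjustment to a different scale from the margin.

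Three stronger readings are also tempting, and the documents do not support them.

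- **That Fisher's exact and chi-square tests decide the primary question.** They belong to a general list for categorical outcomes. The decision rests on the confidence interval.
- **That the decision rule has a scale error.** Margin, rule and primary effect measure are all absolute, and nowhere is an odds ratio used to judge non-inferiority. The limitation is that no adjusted result is available on the scale of the rule.
- **That ignoring the strata brings power down to about 70%.** That level comes from sizing at one-sided 5% and then reading a 95% CI, if that CI is two-sided. It is a separate matter, and the first row of the step 3 table shows it with no stratum effect at all.

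The article also plans a multilevel Cox model for time to symptom resolution. Because it does not name the levels, the lack of a multilevel model for the primary endpoint is no contradiction.

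**Conclusion.** The point holds as a modest, nearly free improvement. Randomisation uses site and age; the Analysis section does not bring them into the primary risk difference, and the one adjusted estimate it describes cannot be compared with 10 points without fixing a control rate. The consequence is a possible small loss of efficiency and the lack of an adjusted answer on the scale of the margin. It is not a risk of falsely claiming non-inferiority, because a crude interval is valid to slightly conservative. The gain from stratifying is about 0 to 1 point of power for stratum rates spanning up to about 24 points, about 2 to 3 for fairly strong spreads, and 5 to 6 only for extreme ones. These gains rest wholly on assumed differences between strata. The odds ratio equivalents follow from arithmetic alone.

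**What to change.** State in the Analysis section, before any unblinded analysis:

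1. The primary estimate is the risk difference (watchful waiting minus antibiotics) stratified by site and age band with Mantel-Haenszel weights, and its 95% CI is compared with −10 points.
2. A pre-specified rule for pooling sparse strata, for instance merging small sites when a site-by-age stratum is empty in one arm. With 396 evaluable children in 12 strata the average is 33 per stratum, and some will be smaller.
3. Any covariate-adjusted result from the logistic model is reported also as a standardised (marginal) risk difference with its CI, next to the odds ratio. The covariates are named.
4. The crude risk difference is kept as a sensitivity analysis.

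The cost is a few sentences and a few lines of code, with no new data and no change to sample size. If the analysis plan already specifies this, it is enough to confirm it and align the protocol wording.
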